#### ***Secondary Endpoints***

Additional QoL endpoints will be analyzed by compiling relevant EQ-5D values, FACT subscale and trial outcome index (TOI) scores. Treatment arm differences will be analyzed using linear mixed-effects models. Survival will be calculated Kaplan-Meier method with differences compared using the stratified log-rank test. Differences in rates of grade 2 or higher toxicity between groups will be tested using the Fisher's Exact test. Differences in the number of cycles of further systemic therapy will be tested using the student's t-test. EQ-5D measurements will be converted into utilities to inform cost-effectiveness/utility analyses. Finally dosimetric comparison of GTV, PTV, as well as standard pulmonary and esophageal metrics will be compared using the student's t-test.

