## **1.0 INTRODUCTION**

### **1.1 Background**

Palliative thoracic radiotherapy is an effective modality for symptom prevention and improvement in patients with metastatic non-small cell lung cancer. For a subset of these patients with good performance status (ECOG 0-1), a meta-analysis found that employing doses of 35 Gy10 and higher (e.g. 30 Gy in 10 fractions) through a standard conventional antero-posterior/postero-anterior (APPA) approach was associated with a modest survival benefit at 1-year, compared to lower doses. This however, was at the cost of an increased rate of esophagitis within 3 months (1). Esophagitis can lead to pain, weight loss, and hospital admissions, and overall can reduce quality of life. In some cases, specifically in the setting of stage III NSCLC, severe esophagitis after treatment has been associated with inferior overall survival (2), perhaps due to malnutrition.

In the modern era, there is wider availability of advanced radiotherapy techniques (e.g. CT-simulation, IMRT, arc-based therapy), allowing for increased conformality and sparing of organs at risk (OARs), allowing for conformal avoidance of organs at risk, such as the esophagus. Esophageal sparing has been employed for stage III NSCLC with early promising results (3,4), but to our knowledge has not been formally tested in the palliative setting. The goal of this study is to conduct a multi-institutional randomized phase III clinical trial comparing standard palliative treatment (APPA), using doses of 20 Gy in 5 fractions or 30 Gy in 10 fractions, versus the same dose using esophageal-sparing IMRT (ES-IMRT).

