#### **Secondary Endpoints:**

1. Pulmonary and General Quality of life
  - Pulmonary quality of life measured by the Lung Cancer Subscale (LCS) of the FACT-L
  - General quality of life measured by the FACT-G and the EQ-5D
2. Overall survival
  - Defined as time from randomization to death from any cause.
3. Toxicity
  - Assessed by the NCI-CTC v.4
4. Cost Effectiveness
5. Dosimetric comparisons of plans in both arms.

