### **3.0 STUDY DESIGN**

This study is designed as a randomized phase III study. Patients will be randomized between standard of care palliative thoracic RT vs. ES-IMRT.

Patients will be stratified by intended dose prescriptions of 30 Gy in 10 fractions or 20 Gy in 5 fractions, and the choice of dose is pre-specified before randomization.

Patients will be randomized in a 1:1 ratio to either:

**Arm 1: Standard Radiotherapy (delivered as 3-D conformal radiotherapy without esophageal sparing).** An APPA technique is preferred.

**Arm 2: Esophageal Sparing Radiotherapy using IMRT.** Patients will receive the same pre-specified dose, but with esophageal sparing.

**In either arm, radiotherapy must begin no later than 2 weeks from the time of randomization, although treatment as early as possible is highly encouraged.**

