### **4.0 PATIENT SELECTION**

#### **4.1 Inclusion Criteria**

1. AJCC 7th edition stage IV NSCLC or stage III not eligible for curative intent treatment
2. Intended to receive palliative radiotherapy to the thorax, to a dose of 30 Gy

in 10 fractions or 20 Gy in 5 fractions. In either treatment arm, at least **5 cm of the esophagus** should be in the intended treatment field.

3. Willingness and ability to provide informed consent
4. ECOG performance status 0-3
5. Age 18 years or older
6. Prior or planned systemic treatment (chemotherapy, immunotherapy, targeted agents) is permissible at the discretion of the treating medical oncologist, provided that no systemic treatment is given within 2 weeks prior to RT, concurrent with RT, or within a 2-week period post RT.
7. Concurrent palliative RT to other metastatic sites is permissible other than the stomach and/or liver
8. Life expectancy > 3 months

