### **5.0 PRE-TREATMENT EVALUATION**

The following are mandatory:

- i. History and physical examination, with documentation of weight and performance status (ECOG)
- ii. CT chest within 3 months.
- iii. Bone scan and brain imaging (CT or MRI) are recommended if there are signs or symptoms consistent with metastases at those sites
- iv. Negative serum or urine pregnancy test for women of child-bearing age
- v. Histological confirmation of NSCLC malignancy
- vi. Informed consent

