### 10.3 Stratification

The sample size calculated allows for one stratification factor at randomization, which will be the prescribed dose (20 Gy/5# vs. 30 Gy/10#).

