### 10.4 Sample size calculation

Regarding the primary endpoint, a change in ECS score of 2 to 3 points is considered clinically relevant. We will assume there will be a moderately large effect size (0.65), and a non-responder rate of 15% (5). Using a two-sided, independent-sample t-test with an alpha level of 0.05 and power of 80%, to detect a clinically relevant ECS change in the experimental arm, 90 patients will be required (45 in each arm).

We anticipate that 1-2 patients could be accrued each month at each participating institution, yielding approximately 30 patients per year. The study thus projects accrual over 4 years with 12 months of additional follow-up. Accrual for the sample size calculated is feasible in the Canadian multi-institutional context.

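### The survival comparison makes no use of baseline ECOG, which must be recorded for every patient; prespecifying an ECOG-adjusted comparison would guard against chance imbalance at almost no cost

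*Protocol*

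**What the plan says.** Overall survival is a secondary endpoint: "Defined as time from randomization to death from any cause" (Protocol 2.1). Section 10.5 gives its only between-arm comparison: "Survival will be calculated Kaplan-Meier method with differences compared using the stratified log-rank test". That sentence does not list the strata.

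Stratification is described elsewhere, always by dose. Section 3.0: "Patients will be stratified by intended dose prescriptions of 30 Gy in 10 fractions or 20 Gy in 5 fractions". Section 10.3: "The sample size calculated allows for one stratification factor at randomization, which will be the prescribed dose". Section 10.1 says the same.

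On performance status, section 4.1 admits "ECOG performance status 0-3". Section 5.0 lists as mandatory before treatment: "History and physical examination, with documentation of weight and performance status (ECOG"). ECOG appears neither in the randomization nor in the survival analysis.

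**The concern.** Performance status may well predict survival in this population, it varies widely under the eligibility criteria, and it will be on file for every patient. With 45 patients per arm and no balancing on ECOG, the arms can differ on it by chance. A dose-stratified test then carries part of that difference into the survival comparison.

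Survival is secondary, but it is a stated objective (section 2.0). In Arm 2 the esophagus takes priority over PTV coverage (section 6.2), so survival is one of the outcomes on which a cost of sparing could appear. If an ECOG gap emerges, readers will ask whether the survival result reflects it, and an adjustment chosen after seeing the data is less convincing than one fixed beforehand.

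**Working it through.** **1. The plan's own figure.** Section 10.4 sizes the trial on the esophageal subscale: "Using a two-sided, independent-sample t-test with an alpha level of 0.05 and power of 80"%, with effect size 0.65 and 15% non-responders. Per arm: 2 × (1.960 + 0.842)² / 0.65² = 37.2, so 38. Total: 76 / 0.85 = 89.4, so 90. The stated 90 reproduces. The protocol gives no event count, hazard ratio or power for survival.

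**2. How large a chance imbalance is.** Assumption: a share p of patients is ECOG 2-3. The SD of the between-arm difference is sqrt(2p(1−p)/45).

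| p | SD (points) | P(gap ≥ 10) | P(gap ≥ 15) | P(gap ≥ 20) |
|---|---|---|---|---|
| 20% | 8.4 | 24% | 7.5% | 2% |
| 30% | 9.7 | 30% | 12% | 4% |
| 40% | 10.3 | 33% | 15% | 5% |
| 50% | 10.5 | 34% | 16% | 6% |

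**3. What it does to the estimate.** A gap d shifts the hazard ratio by roughly exp(d × ln h), where h is the ECOG hazard ratio. For h from 1.5 to 2.5 the factor is 1.04-1.10 at 10 points and 1.08-1.20 at 20 points.

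**4. What it does to the test when there is no treatment effect.** Simulation of 4,000 trials of 90 patients per setting. Assumptions, none from the protocol: median survival 8 months, exponential survival, follow-up 12-48 months, doses split equally and not prognostic. Deaths averaged 77-80.

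| ECOG HR | ECOG 2-3 share | Error, all trials: dose strata / dose × ECOG strata | Error, gap ≥ 15 points: dose strata / dose × ECOG strata |
|---|---|---|---|
| 1.5 | 30% | 5.4% / 5.1% | 6.9% / 4.7% |
| 1.5 | 50% | 5.0% / 5.4% | 6.1% / 5.7% |
| 2 | 30% | 5.2% / 5.1% | 7.7% / 5.5% |
| 2 | 50% | 4.7% / 5.3% | 7.4% / 5.4% |
| 3 | 30% | 5.6% / 5.1% | 7.7% / 5.4% |
| 3 | 50% | 5.8% / 5.0% | 12.0% / 4.7% |

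The correlation between the test statistic and the ECOG gap is 0.17-0.46 with dose strata and about 0 once ECOG is included. The last column rests on the 12-17% of trials with such a gap, about 490-690 trials, so its Monte Carlo error near 5% is sqrt(0.05 × 0.95 / 490) = 1.0 point at most. At an ECOG hazard ratio of 1.5 the excess over 5% is therefore barely distinguishable from noise.

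**5. Power.** The first two result columns use the simulation above (dose strata → dose × ECOG strata). The third is a separate set of 2,000 trials with follow-up cut at 12 months, about 58 deaths and 40% ECOG 2-3 (dose-stratified log-rank → dose-stratified Cox adjusted for ECOG).

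| ECOG HR | Arm HR 0.65 | Arm HR 0.55 | Arm HR 1.75 |
|---|---|---|---|
| 1.5 | 43-44% → 43% | 68% → 67% | 60.3% → 61.1% |
| 2 | 40-41% → 42% | 63-66% → 66-67% | 56.2% → 61.2% |
| 3 | 33-34% → 40-41% | 57-59% → 66-67% | 48.2% → 59.2% |

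Setting by setting, the gain is within Monte Carlo error of zero at 1.5, 1-5 points at 2, and 6-11 points at 3. In the Cox set the type I error was 4.3-5.1%. Conditional error was computed with ECOG as a stratum, not as a Cox covariate.

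**6. Survival power overall.** With 75 deaths and arm hazard ratio 0.65: 0.431 × sqrt(75) / 2 − 1.96 = −0.09, giving 46% power. For 80%, 4 × (1.960 + 0.842)² / 0.431² gives 170 deaths, more than the 90 patients enrolled.

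**The case against.** The planned test is standard, valid and consistent with the randomization, and covariate adjustment of a secondary endpoint is often left to a SAP, which is not at hand. It is fair to call this an improvement and not an error. Still, the protocol names one survival comparison, and that comparison leaves out a covariate the protocol already requires.

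The shift is also modest against the noise. In the 58-death set, a 15-point gap moves the log hazard ratio by 0.07-0.16, while its standard error is about 2 / sqrt(58) = 0.26, so the shift is 0.3-0.6 of a standard error. This stands, and it limits the weight of the point.

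Several stronger readings are tempting, and the documents do not support them:

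- **The protocol states stratification by dose alone.** It does not name the log-rank strata; dose is inferred from sections 3.0, 10.1 and 10.3.
- **Power is lost.** That depends on an ECOG hazard ratio the protocol does not give; at 1.5 there is no loss.
- **The log-rank analysis understates the arm effect.** The unadjusted hazard ratio is marginal and the adjusted one conditional. They differ through non-collapsibility, which is not bias.
- **The Background shows ECOG to be prognostic.** The passage beginning "For a subset of these patients with good performance status (ECOG 0-1") concerns the effect of dose within that subgroup. It gives no prognostic effect of ECOG, and a main-effect adjustment would not address an interaction with dose.
- **Stage should be adjusted for as well.** Stage III and IV are both eligible, but no figure in the protocol and no simulation here shows a gain.

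**Conclusion.** The point holds as a low-cost improvement to a secondary analysis. The planned test keeps its overall error near 5%, so a reader should not infer that it is invalid. The weakness is conditional: in the roughly 8-16% of trials with an ECOG gap of 15 points or more (for 20-50% at ECOG 2-3), type I error rises to about 6-12%, and including ECOG brings it back to 5-6%. The upper end needs a strongly prognostic ECOG (hazard ratio 3) and half the patients at ECOG 2-3.

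Any power gain follows the same unknown prognostic strength, from none to about 11 points. It does not rescue survival, which remains underpowered. The ECOG mix, ECOG hazard ratio, median survival and arm hazard ratios are all assumptions. The primary endpoint and the sample size of 90 are untouched.

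**What to change.** In Protocol 10.5, and in the SAP if there is one:

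- State that the log-rank test is stratified by prescribed dose.
- Prespecify as the survival comparison a Cox model stratified by prescribed dose and adjusted for baseline ECOG (0-1 v 2-3), reported as a hazard ratio with 95% CI and described as conditional on ECOG.
- Keep the dose-stratified log-rank test and the Kaplan-Meier curves as supportive results.
- Treat stage (III v IV) as an optional covariate only.

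The cost is a sentence or two. No new data, visits or patients are needed, because ECOG is already mandatory before treatment. The one consequence to manage is interpretation: the hazard ratio becomes conditional on ECOG, and the report must say so.

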#### **6.1 Standard Arm (Arm 1)**

RT for patients in the standard arm should adhere to the principles of palliative RT, with goals of alleviating symptoms or preventing potential complications. An APPA parallel-opposed pair (POP) beam arrangement is favored wherever possible. POP fields will be placed to encompass PTV (without regard for ES-PTV). Multileaf collimator blocks may be placed to protect OARs (i.e. lung) at the discretion of the treating physician.

Dosimetric parameters for Arm 1 are as follows:

- **The field edge should be >5 mm from the edge of PTV.** If the oncologist feels that the resulting field size is larger than required, then smaller target volumes should be defined. It is not necessary to contour areas of disease that are not being treated.
- The maximum effective field size is recommended to be limited to **225 cm^2** but is at the discretion of the treating radiation Oncologist. The maximum hot spot is limited to no more than a 2 cm^3 contiguous volume receiving 115% or more of the prescribed dose.

The treating physician, dosimetrist or physicist will record the following parameters from the APPA fields:

- length of esophagus in the field (defined as the length of esophagus receiving >50% of the prescription dose at any point along its circumference). This is required to be at least 5 cm for enrollment.
- maximum and mean esophageal dose
- maximum cord dose
- PTV D95 (the dose to the hottest 95% of the PTV).
- Lung eval V16 (if 30 Gy in 10 fractions used) or V13 (if 20 Gy in 5 fractions used).
  - The V16 and V13 are used to approximate the V20 used for conventional fractionations. BED values are as follows:
    - When V20 is used with a prescription dose of 60 Gy in 30

fractions, the corresponding BED, for the 20 Gy in 30 fractions received by lung eval, is 24.4 Gy3

- When V16 is used with a prescription dose of 30 Gy in 10 fractions, the corresponding BED, for the 16 Gy in 10 fractions received by lung eval, is 24.5 Gy3
- When V13 is used with a prescription dose of 20 Gy in 5 fractions, the corresponding BED, for the 13 Gy in 5 fractions received by lung eval, is 24.2 Gy3

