## 6.2 Experimental Arm (Arm 2)

The GTVs and PTVs used for planning in Arm 2 are those that have been defined in Arm 1 for that particular patient. Patients randomized to Arm 2 will undergo IMRT planning. Treatment can be delivered using static beams (either 3D-conformal radiotherapy, or intensity-modulated) or rotational therapy (volumetric modulated arc therapy, or tomotherapy). Priority will be placed on generating clinically acceptable plans while minimizing complexity, planning time and treatment time.

ES-PTV will be optimized and the esophagus will take priority over PTV in the optimization process. In most cases, ES-PTV will need to be compromised in order to achieve esophageal constraints.

For plans in Arm 2, dose constraints are as follows:

- The maximum dose within the body is limited to no more than 2 cm^3 receiving 115% or more of the prescription dose.
- The allowable dose to “lung\_eval” is based on the values from the fields placed for that particular patient. The V16 value (for 30 Gy in 10 fractions) or the V13 value (for 20 Gy in 5 fractions) may not exceed the value recorded from the APPA fields by more than 3%. For example:
  - if a patient has a V16 value of 30% with the APPA fields (prescription dose 30 Gy in 10 fractions), the V16 value with the IMRT plan may not exceed 33%.
  - if a patient has a V13 value of 30% with APPA fields (prescription dose 20 Gy in 5 fractions), the V13 value with the IMRT plan may not exceed 33%
  - For all patients, the V5 should be less than 60%.
- The dose to the esophagus should be as low as achievable. Underdosage of the PTV is allowed and will often be required. The following approach should be used:
  - **Step 1: A plan is designed constraining the maximum dose to the esophagus to 80% of the prescription dose** (i.e. 24 Gy if using 30 Gy in 10 arm and 16 Gy if using 20 Gy in 5 fractions). This constraint is met regardless of GTV and PTV coverage within the Esophagus\_ring. In some cases, if there is GTV within the Esophagus\_ring, small areas of that GTV may receive as little as 80% of the prescription dose.
    - 95% of the ES-PTV outside of the Esophagus\_ring should still

receive at least the same D95 as in Arm 1. Better PTV coverage is allowed as long as lung constraints are met.

- **Notes:** suggested optimization parameters will be provided. The maximum esophageal dose is defined as the dose to the hottest 0.1 cc.

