- **Step 2. Once this is achieved, the dose to the esophagus should be further reduced if possible**, while ensuring that all GTV within the Esophagus\_ring receives at least 80% of the prescription dose, and 95% of all ES-PTV outside the Esophagus\_ring receives at least 95% of the prescription dose.

#### 6.2.1 Example Plans for Arm 2

The plans on the following page demonstrate the esophageal sparing technique for two cases prescribed 30 Gy in 10 fractions, one where the GTV is in close proximity to the esophagus (left) and one not in close proximity (right). Structures are: GTV (blue), PTV (red), esophagus (green). The same color scheme applies for the DVHs, with the “lung evaluation” structure in light blue, the dotted lines representing the IMRT plan, and the solid line representing the APPA plan.

Notes:

- i. The fields in Arm 1 should represent the fields that would be used in standard clinical practice, and dosimetric coverage of GTV and PTV is not protocol-specified.
- ii. In the plan at left, esophageal sparing stops once <0.1 cc of esophagus is receiving ≤80% of the prescription dose. This ensures that the GTV adjacent to the

esophagus receives at least 80% of the prescription dose. In the plan at right, more esophageal sparing can be achieved.

- iii. For this prescription, V16 is the parameter of interest for the lung evaluation structure. The V16 in the IMRT plan cannot be >3% more than in the APPA plan, and the V5 must remain below 60%
- iv. In some cases, PTV coverage is better with IMRT than with the standard clinical fields. This is allowed, but not required.
- v. In a situation where the esophagus is abutting the GTV, GTV underdosage (<80% of the prescription dose) is permissible, provided that this volume is <1cc.

[figure not shown]

**Figure 2: Esophageal Sparing for two cases prescribed 30 Gy in 10 fractions, one where the GTV is in close proximity to the esophagus (left) and one not in close proximity (right). Legend: GTV (blue), PTV (red), esophagus (green). The same color scheme applies for the DVHs, with the “lung evaluation” structure in light blue, the dotted lines representing the IMRT plan, and the solid line representing the APPA plan.**

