## **10.0 STATISTICS AND SAMPLE SIZE CALCULATIONS**

### 10.1 Randomization

Patients will be randomized in a 1:1 ratio between Arm 1 and Arm 2. The sample size allows for one stratification factor at randomization: the prescribed RT dose. Randomization will occur in permuted blocks, with the block size known only by the statistician.

A randomized design is indicated for the following reasons:

1. Historically, esophagitis following RT for lung cancer has been measured mostly

through CTCAE, and such data may not provide an appropriate control due to various sources of biases from patient selection, technical RT factors and other comparisons. Thus randomization will provide a more appropriate control group to serve for the experimental arm, particularly when using the FACT-G and cancer subscales.

2. The sample size calculated allows for adequate power to detect a clinically meaningful change in esophageal quality of life

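### The dosimetric endpoint is tested with an unstratified t-test across two prescriptions; this costs precision if doses are analysed in Gy, but does not bias the comparison

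*Protocol*

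**What the plan says.** The protocol lists dosimetric comparison of plans as a secondary endpoint (Section 2.1). Section 10.5 fixes the method: "Finally dosimetric comparison of GTV, PTV, as well as standard pulmonary and esophageal metrics will be compared using the student's t-test". It gives no unit and no stratum term. In the same paragraph survival is analysed with "differences compared using the stratified log-rank test".

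Prescription is the only stratification factor. Section 3.0 states: "Patients will be stratified by intended dose prescriptions of 30 Gy in 10 fractions or 20 Gy in 5 fractions". Sections 10.1 and 10.3 repeat this, with 1:1 allocation; on method, 10.1 says "Randomization will occur in permuted blocks, with the block size known only by the statistician".

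Section 6.1 lists what is recorded from the APPA fields, including maximum and mean esophageal dose and PTV D95. For lung, the recorded metric depends on the prescription: "The V16 and V13 are used to approximate the V20 used for conventional fractionations". Section 6.2, Step 1, sets the Arm 2 esophageal limit relative to prescription: "A plan is designed constraining the maximum dose to the esophagus to 80% of the prescription dose", that is, "24 Gy if using 30 Gy in 10 arm and 16 Gy if using 20 Gy in 5 fractions". Step 2 adds that "the dose to the esophagus should be further reduced if possible".

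**The concern.** Doses to esophagus and target scale with the prescription, and the trial mixes two prescriptions in a ratio of 3 to 2. A t-test without the stratum counts that built-in spread as residual noise. Randomization has already balanced it between the arms, so the estimated standard error is larger than the true one.

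At stake is the endpoint that documents whether esophageal sparing was delivered and what it cost in target coverage. That evidence helps in reading either a positive or a null quality-of-life result. Smaller contrasts, such as differences in PTV coverage or a modest change in mean esophageal dose, could be missed. A single pooled difference in Gy would also be hard to interpret at either dose level.

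**Working it through.** **Inputs from the protocol.** Prescriptions of 30 and 20 Gy, allocation 1:1 and stratified by prescription (3.0, 10.1, 10.3). Arm 2 esophageal maximum limited to 80% of prescription (6.2, Step 1). 45 patients per arm (10.4).

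**Assumptions, not in the protocol.** Doses are analysed in Gy. Half the patients are on each prescription. Esophageal maximum averages 100% of prescription in Arm 1 and 80% in Arm 2. Within-stratum SD is a fixed percentage of prescription, the same in both arms.

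**1. The protocol's own figures.** The limits reproduce: 0.80 × 30 = 24 Gy and 0.80 × 20 = 16 Gy. The sample size, which concerns only the primary endpoint, also reproduces: an effect size of 0.65 with two-sided alpha 0.05 and 80% power needs 38 per arm by the normal approximation, 76 in total, and 76/0.85 = 89.4, rounded up to 90. No power is stated for dosimetry.

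**2. Pooled difference.** Arm 1 mean = (30 + 20)/2 = 25 Gy. Arm 2 mean = (24 + 16)/2 = 20 Gy. The pooled difference is 5 Gy; the stratum differences are 6 Gy and 4 Gy.

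**3. Variance from the dose mix.** For two groups with share p on the higher dose, variance = p(1 − p) × (gap)². Arm 1: 0.25 × 10² = 25. Arm 2: 0.25 × 8² = 16. Average: 20.5 Gy².

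**4. Confidence interval width.** Within-stratum variance W = 0.5 × [(s × 30)² + (s × 20)²]. Ratio of widths = √((20.5 + W)/W). Unstratified SE = √(2 × (20.5 + W)/45).

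| s | W (Gy²) | 20.5 + W | CI ratio | Unstratified SE (Gy) | t for 5 Gy |
|---|---|---|---|---|---|
| 5% | 1.625 | 22.125 | 3.69 | 0.99 | 5.0 |
| 10% | 6.5 | 27.0 | 2.04 | 1.10 | 4.6 |
| 15% | 14.625 | 35.125 | 1.55 | 1.25 | 4.0 |

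These ratios use the pure within-stratum variance. A linear model in Gy with arm and dose level but no interaction leaves residuals of ±0.5 Gy in the cell means (fitted 29.5, 20.5, 24.5, 15.5 against 30, 20, 24, 16). That adds 0.25 to W, and the ratios become 3.44, 2.00 and 1.54. With 70% of patients on 30 Gy, the pure within-stratum ratios are 3.2, 1.8 and 1.4.

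**5. Calibration and power.** 20,000 simulated trials per scenario, 45 per arm, 22 on 30 Gy and 23 on 20 Gy in each arm. The comparator is a t-test on percentage of prescription, which removes the between-prescription spread. Entries are unstratified Gy test / comparator.

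| s | Type I error | Power, 10% reduction | Power, 20% reduction |
|---|---|---|---|
| 5% | 0.000 / 0.050 | 93% / 100% | 100% / 100% |
| 10% | 0.000 / 0.049 | 65% / 99.7% | 100% / 100% |
| 20% | 0.006 / 0.050 | 35% / 65% | 97.5% / 99.7% |
| 30% | 0.018 / 0.048 | 21% / 34% | 79% / 88% |

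Under no effect, the mean estimated difference stayed within 0.02 Gy of zero, so there is no bias. A chance imbalance of one patient between arms in the dose mix moves the mean by 10/45 = 0.22 Gy.

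**The case against.** The strongest reply is that this changes nothing important. The unstratified test is valid, its error is on the safe side, and the planned 20% contrast gives t of 4.0 or more in every row of the first table. That stands, and it limits the point to a minor one.

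A reader might infer more than the protocol supports:

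- **That the protocol analyses unscaled Gy.** It is silent on the unit. The Section 6.1 list is a data-capture list, and many of the protocol's dose criteria are already percentages of prescription. The analysis plan, not shown, may set the unit. The choice of test, however, is stated in the protocol and not deferred.
- **That pooling biases the comparison.** It does not, because allocation is 1:1 within prescription.
- **That a spared 30 Gy patient is ranked as more exposed than an unspared 20 Gy patient.** In Gy, 24 does exceed about 20, but only for maximum dose exactly at the limit. Step 2 can lower it, and nothing fixes the mean dose. A t-test compares arm means, not two chosen patients. In biologically effective dose the order depends on alpha/beta: 24 × (1 + 2.4/10) = 29.8 against 20 × (1 + 4/10) = 28.0 Gy10, but 24 × (1 + 2.4/3) = 43.2 against 20 × (1 + 4/3) = 46.7 Gy3.
- **That the stratified log-rank test makes this an internal contradiction.** It does not. The same paragraph uses other unstratified tests. It shows only that the stratum was considered for one endpoint.

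Cord dose is recorded but is not among the metrics named for comparison in 10.5, so the point does not extend to it. The lung V16 and V13 are already chosen by prescription, so the Gy-scale argument does not apply to them in the same way.

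**Conclusion.** The point holds as a loss of efficiency. Section 10.5 commits a dose endpoint to a test that ignores the one stratification factor, which also sets the dose scale. If the analysis is in Gy, the interval is about 3.7 to 1.5 times as wide as a stratified one for within-stratum SDs of 5% to 15%, type I error falls well below 0.05, and power for a 10% reduction drops (65% against 99.7% at an SD of 10%). A 20% reduction is still detected with high power unless the within-stratum SD is near 30% (79% against 88%). If the analysis uses percentage of prescription, most of the problem disappears. The size rests on the assumed unit, split, arm means and SDs, none of which the protocol gives. The point is minor and affects only this secondary endpoint.

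**What to change.** In Section 10.5, replace the Student's t-test for dosimetric metrics with a comparison that takes prescribed dose as a stratum, for example a linear model with arm and dose level, and state the unit of each metric. Report results in Gy separately for 20 Gy in 5 and 30 Gy in 10.

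Expressing doses as a percentage of prescription is an optional presentation choice, not a correction: Gy, percentage and biologically effective dose answer different questions.

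The cost is a sentence of analysis wording. Prescription is known before randomization and the doses are already recorded, so no data collection, sample size or treatment changes.

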#### **Heart**

- contoured from the apex of the heart to the inferior aspect of the origination of the ascending aorta

**Prior to randomization, the intended APPA fields from Arm 1 will be placed on the planning CT, and that plan will be signed by the radiation oncologist. Those fields will be used as the basis for safe toxicity parameters for Arm 2. If the patient is randomized to Arm 1, the signed fields are to be treated without further modification.**

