### 6.4 Central Collection of Imaging Data

Imaging data will be centrally collected through the Quantitative Imaging for Personalized Cancer Medicine (QIPCM) platform ([qipcm.technainstitute.com](http://qipcm.technainstitute.com)), which provides centralized storage and data analysis tools for medical imaging, and is compliant with national and international privacy regulations. Scans collected by QIPCM will include the planning scan, POP and ES-IMRT radiation dose distributions, and baseline/follow-up CTs of the thorax. Note the follow-up CTs are optional, but those performed will be collected through QIPCM. Participating sites will be provided separate instructions regarding the uploading procedure.

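### The dosimetric endpoint is assigned a plain Student's t-test, most naturally read as between arms, although every Arm 2 patient has both plans on the same anatomy and a paired test would be more precise at no cost

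*Protocol*

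**What the plan says.** The dosimetric endpoint is the last secondary endpoint in Protocol section 2.1: "Dosimetric comparisons of plans in both arms". Section 10.5 assigns its test: "dosimetric comparison of GTV, PTV, as well as standard pulmonary and esophageal metrics will be compared using the student's t-test". No pairing, covariate or dose stratum is mentioned for it, although survival in the same paragraph gets a stratified log-rank test.

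The planning sections describe how the data arise:

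- Section 6.04 (end): "Prior to randomization, the intended APPA fields from Arm 1 will be placed on the planning CT, and that plan will be signed". For Arm 1 it adds: "If the patient is randomized to Arm 1, the signed fields are to be treated without further modification".
- Section 6.1: "The treating physician, dosimetrist or physicist will record the following parameters from the APPA fields". The list covers length of esophagus in the field, maximum and mean esophageal dose, maximum cord dose, PTV D95, and lung V16 or V13. It contains no GTV metric.
- Section 6.2: "The GTVs and PTVs used for planning in Arm 2 are those that have been defined in Arm 1 for that particular patient". Only Arm 2 receives an IMRT plan.
- Section 6.4: the scans held centrally include the planning scan and the "POP and ES-IMRT radiation dose distributions".

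**The concern.** Tumour size and position differ widely between patients and drive much of the spread in esophageal, lung and target dose. A test between two groups of different patients carries all of that spread. A comparison of two plans for the same patient removes the part they share. The design creates those pairs for every Arm 2 patient, and the planning rules already rely on them: section 6.2 limits an IMRT plan's lung V16 or V13 relative to that patient's own APPA value. The analysis as most naturally read does not use the pairing.

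At stake is the precision with which the trial can describe what sparing costs in lung dose and target coverage. Neither the primary endpoint nor the validity of the dosimetric test is in question.

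**Working it through.** **Inputs.** 45 patients per arm, two-sided alpha 0.05 and 80% power (section 10.4). Not in the protocol, so assumed: the within-patient correlation r between APPA and ES-IMRT values, and the SDs of the metrics.

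**The plan's own figure.** No sample size is given for the dosimetric comparison. The trial's 90 reproduces: 2 × (1.960 + 0.842)² / 0.65² = 37.2, rounded up to 38 per arm; 38 / 0.85 = 44.7, rounded up to 45 per arm.

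**Standard errors, equal SDs.**

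- Unpaired, 45 against 45: SD × √(2/45) = 0.211 SD.
- Paired, 45 Arm 2 patients: SD × √(2(1 − r)/45).
- Ratio, paired to unpaired: √(1 − r).

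| Assumed r | Paired SE (SD units) | Ratio | Detectable difference at 80% power (SD units) |
|---|---|---|---|
| 0 | 0.211 | 1.00 | 0.60 |
| 0.3 | 0.176 | 0.84 | 0.51 |
| 0.5 | 0.149 | 0.71 | 0.43 |
| 0.8 | 0.094 | 0.45 | 0.27 |

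The unpaired test detects 0.60 SD.

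**Unequal SDs.** The ratio becomes √(1 − 2r·s₁s₂/(s₁² + s₂²)). If one SD is half the other, this is √(1 − 0.8r): 0.77 at r = 0.5 and 0.60 at r = 0.8. The gain shrinks but remains.

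**Maximum esophageal dose.** Assume about 100% of prescription in Arm 1 against the 80% cap in section 6.2, a difference of 20 points. Unpaired power with 45 per arm is above 99% for an SD up to 20 points and 88% for an SD of 30 points. Pairing adds little here.

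**Lung V16/V13.** Section 6.2 lets the IMRT value exceed the patient's own APPA value by 3%; its 30%-to-33% example shows that percentage points are meant. Power to detect a mean shift of 3 points, with the SD assumed:

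| Assumed SD (points) | Unpaired | Paired, r = 0.5 | Paired, r = 0.8 |
|---|---|---|---|
| 8 | 42% | 69% | 97% |
| 10 | 29% | 50% | 87% |
| 15 | 16% | 26% | 55% |

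A non-significant unpaired lung result could therefore coexist with the largest mean increase that the planning rule allows.

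**Pooling the two prescriptions.** If esophageal or target doses are analysed in Gy, an assumed 50:50 mix of 20 and 30 Gy has an SD of 5 Gy from prescription alone. At 100% against 80% of prescription, the mean difference is 5 Gy and the mixing SDs are 5 and 4 Gy, so the pooled SD is √((25 + 16)/2) = 4.5 Gy. Unpaired power is still 99.9%; it is 99% with a further 3 Gy of between-patient SD and 94% with a further 5 Gy. Mixing adds avoidable noise but does not sink this contrast. It does not apply to V16 and V13, which are volume percentages already matched on BED between the prescriptions (24.5 and 24.2 Gy₃, section 6.1).

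**The case against.** **The test may be paired.** Section 10.5 says only Student's t-test, whereas section 10.4 specifies independent samples for the primary endpoint. A reader might infer that an unpaired test is fixed. The text does not say so; that reading rests on the endpoint definition in section 2.1 and on the group comparisons elsewhere in section 10.5. This stands as a limit on the point.

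**This is detail for an analysis plan that is not shown.** Partly fair. But the protocol does name a test for this endpoint, and the point is that the design supports a better one.

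**The randomized comparison is valid, and a paired one answers a different question.** The first half stands: there is no bias, and randomization is stratified by dose. The second half does not. Arm 1 is treated with the signed fields unmodified, so an Arm 2 patient's own APPA plan is what Arm 1 would have delivered to that patient. Both contrasts estimate the same effect of technique.

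**Nothing is lost.** A reader might infer that the paired data are discarded. They are not: the dose distributions are kept centrally, so the paired analysis stays available.

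**The gain is assumed.** Correct. The cap on esophageal dose could compress the IMRT spread and lower the correlation, and at r = 0 there is no gain. A claim that the trial cannot show whether sparing was achieved would go too far, given the power for maximum esophageal dose.

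**Conclusion.** The point holds as a minor loss of efficiency on the last-listed secondary endpoint. Read as between-arm, the test is valid but has a larger standard error than a paired comparison for any positive within-patient correlation. With equal SDs, the paired standard error is 84%, 71% and 45% of the unpaired one at r of 0.3, 0.5 and 0.8. The direction follows from the design. The size rests on correlations and SDs that the protocol does not give. The loss falls mainly on lung V16/V13 and PTV coverage, and hardly on maximum esophageal dose. The primary endpoint and the sample size are unaffected.

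**What to change.** In section 10.5, or in the statistical analysis plan:

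1. Make the dosimetric comparison a paired t-test of ES-IMRT minus own APPA plan in Arm 2.
2. Express esophageal and target dose metrics as a percentage of prescription, or analyse them by dose stratum. Pairing alone does not settle this, because a 20% reduction is 4 Gy in one stratum and 6 Gy in the other.
3. Derive the GTV metrics, which are not on the recorded APPA list, from the centrally stored dose distributions.
4. Keep the between-arm comparison of treated plans as supportive, stratified by prescribed dose. Do not adjust it by ANCOVA for the patient's own APPA value: in Arm 1 the treated plan is that plan, so outcome and covariate are identical by construction.

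The cost is wording and the extraction of GTV metrics from stored files. No further plans, patients or visits are needed.
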